## Abstract

**Background:**

Obsessive-compulsive disorder (OCD) imposes significant burdens on individuals, families, and healthcare systems and the COVID-19 pandemic appears to have exacerbated OCD symptoms. Currently, there are no validated prevention programs for OCD, highlighting a critical gap in mental health services. This study aims to develop and validate the first ØCD prevention program, for at-risk adults, utilizing cognitive-behavioral therapy (CBT) and exposure response prevention (ERP) techniques.

**Methods:**

A single-blind, randomized controlled trial comparing the ØCD prevention program to a waitlist control group will be conducted. Participants, at-risk adults (18–65 years) with subclinical OCD symptoms (OCI-R score ≥ 12), will be recruited for the study. The ØCD prevention program compresise of six online group sessions incorporating CBT and ERP techniques over three modules. The primary outcomes are OCD symptom severity (measured by the Obsessive-Compulsive Inventory- revised form; OCI-R), depression symptoms (measured by the Patient Health Questionnaire; PHQ-9), and anxiety symptoms (measured by the Generalised Anxiety Disorder 7-item; GAD-7). Secondary outcomes include OCD-related beliefs, experiential avoidance, resilience, quality of life, uncertainty intolerance, automatic thoughts, and distress. Outcome measures will be collected at baseline, at completion of the intervention, and one year later (follow-up). At follow-up, we will also analyze the OCD diagnostic incidence, using the Structured Clinical Interview for DSM-5. We will employ a multivariate analysis of variance (MANOVA) to explore whether significant differences exist between groups across dependent variables. To compare the OCD incidence levels from the pre-test to the follow-up we will use the chi-squared test.

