### Primary outcome measures

#### Obsessional Compulsive Inventory - Revised (OCI-R; [10])

OCI-R is a self-report questionnaire of 18 items, and it measures OCD symptoms across six subscales: washing, checking, neutralising, obsessing, ordering, and hoarding. OCI-R was used in the initial screening of eligible participants, where the OCD subscale (which excludes the hoarding component) was used to determine participants who are at risk of developing OCD symptoms (cut off point (≥ 12). For the present study, the reduction in OCI-R OCD subscale assessment is the primary outcomes.

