### Statistical analyses

#### Data analysis

Demographic and clinical data will be reported as means and SDs for continuous parametric data, medians, and ranges for non-parametric data, and frequencies and percentages for categorical data. Only two authors will have access to the final trial dataset. To illustrate participant flow, we will report results in a CONSORT diagram. Data analysis will be conducted using SPSS for Windows version 25. Given the anticipated dropout rate, mixed models will be employed as the most suitable statistical method. This approach is well-suited for analyzing repeated measures, accounting for the dependency between observations and handling missing data effectively. Mixed models will be adjusted for baseline values of the repeated measures. Descriptive statistics will be generated to summarize the means and proportions of baseline clinical and demographic variables across treatment conditions, allowing for the assessment of potential imbalances. Fixed effects in the model will include time, treatment, and their interaction. In cases of missing data, these variables will also be included as fixed effects. The significance of the time*treatment interaction p-values for various outcome measures will be assessed using the Benjamini–Hochberg procedure (two-sided p < 0.05). Time will be treated categorically, with the first post-baseline measurement serving as the reference category. To address the correlation among repeated measurements, a first-order autoregressive (AR (1)) structure will be imposed on the residuals. Furthermore, the interaction effect between time and group will be explored by analyzing estimated marginal means at different time points. We anticipate a significant interaction effect between time and group, signifying differential changes in scores over time between the two treatment conditions. Specifically, we expect a more pronounced decline in scores over time in the prevention group compared to the control group. To assess the statistical significance of improvements in the treatment conditions, a least significant difference test will be conducted with estimated marginal means to compare changes between groups. Linear mixed models are expected to reveal a statistically significant decline in the prevention condition from pretest to post-test, with no significant differences between post-test and follow-up measures. To facilitate comparisons with other studies, Cohen’s d statistic will be calculated to determine within-group effect sizes. In cases where the proportion of missing data exceeds 10%, maximum likelihood imputations will be performed based on demographics and pretreatment scores. Additionally, the proportions of dropouts and diagnostic incidence (from pre-test to follow-up) in the two treatment groups will be compared using the chi-square test.

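### The article plans a MANOVA in the Abstract but mixed models in the Methods, leaves the primary outcome unsettled, and gives the primaries no error control of their own

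*Protocol article*

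**What the plan says.** **Analysis method.** Abstract, Methods: "We will employ a multivariate analysis of variance (MANOVA) to explore whether significant differences exist between groups across dependent variables". Data analysis: "Given the anticipated dropout rate, mixed models will be employed as the most suitable statistical method". That section specifies fixed effects for time, treatment and their interaction, fitted outcome by outcome. It contains no MANOVA.

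**Primary outcome.** Abstract: "The primary outcomes are OCD symptom severity (measured by the Obsessive-Compulsive Inventory- revised form; OCI-R), depression symptoms", and then anxiety on the GAD-7. The hypotheses under Aim of the present study put the same three scales first. In the Methods, OCI-R, PHQ-9 and GAD-7 are parallel entries under Primary outcome measures, but the OCI-R entry says that "the reduction in OCI-R OCD subscale assessment is the primary outcomes". That subscale excludes hoarding. The Abstract does not restrict OCI-R to it.

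**Multiplicity.** Data analysis: "The significance of the time*treatment interaction p-values for various outcome measures will be assessed using the Benjamini–Hochberg procedure (two-sided p < 0.05"). The outcomes that form the family are not listed, and primaries are not separated from secondaries.

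**The concern.** A MANOVA tests one joint hypothesis on a vector of outcomes. The mixed models test a time-by-treatment interaction separately for each scale. These are different hypotheses that handle missing data differently, and they can disagree on the same data.

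The article also leaves open whether success means the joint test, any one of three primaries, all three, or the OCI-R subscale alone. A published protocol should close that choice before the data are seen.

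Benjamini–Hochberg does not close it. It controls the expected share of false claims among all claims made, not the chance of any false claim among the primaries. If primaries and secondaries share a family, the bar for a primary claim also depends on how the secondary scales turn out.

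**Working it through.** **Inputs**
- Three primary scales and seven secondary scales (Abstract; Primary and Secondary outcome measures): 3 + 7 = 10.
- Two-sided 0.05 for Benjamini–Hochberg (Data analysis).
- d=0.3, computed N=175, target 200, i.e. 100 per arm (Sample size).
- Assumed, because the article does not give them: all ten scales in one family; correlation between scales from 0 to 0.7; effect sizes on the secondaries.

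**1. Does the sample size show which analysis is meant?** It does not. A two-arm comparison at d=0.3, two-sided 0.05 and 95% power needs 289 per arm, 578 in total, not 175. If 0.3 is read as Cohen's f (f² = 0.09), a two-group MANOVA on three outcomes needs 195. The figure 175 therefore settles neither the method nor the number of primaries. Its failure to reproduce is a separate matter.

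**2. Threshold for one outcome.** Benjamini–Hochberg rejects the k smallest p-values, where k is the largest rank with p(k) ≤ 0.05 × k/10. The OCI-R threshold is 0.05 × 1/10 = 0.005 if nothing else is rejected, and 0.05 × 10/10 = 0.05 if everything is.

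**3. Three primaries, all null, seven responding secondaries.** If the seven are certain to be rejected, the first null primary to be rejected takes rank 8 and faces 0.05 × 8/10 = 0.04. Under independence the chance of at least one false primary claim is about 1 − (1 − 0.04)³ = 0.115. Simulated values (the two d rows use 100 per arm):

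| Effect on secondaries | correlation 0 | 0.5 | 0.7 |
|---|---|---|---|
| d=0.3 | 6.0% | 5.5% | 5.1% |
| d=0.5 | 10.8% | 8.7% | 6.5% |
| very strong (limit) | about 11.5% | about 10% | 8.9% |

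With N=175 the d=0.5 row falls slightly, to 5.9% at correlation 0.7. For comparison, three unadjusted tests at 0.05 give 1 − 0.95³ = 14.3% under independence.

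**4. OCI-R as sole primary, still inside the family of ten.** Its threshold can never exceed 0.05, so its own false-positive rate cannot exceed 5%. With the other nine scales at d=0.5, simulation gives 4.7% (correlation 0) down to 3.5% (correlation 0.7).

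The cost is in power. For an unadjusted t-test the noncentrality is 0.3 × √(175/4) = 1.98:
- fixed two-sided 0.05: 51%;
- Benjamini–Hochberg, all ten scales responding at d=0.3: about 37–39%;
- only OCI-R moves, threshold 0.005: 20%.

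At N=200 the first and last become 56% and 24%.

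**The case against.** **Three primaries may be the consistent reading.** PHQ-9 and GAD-7 stand under the primary heading and in the main hypothesis, which agrees with the Abstract. The sentence in the OCI-R entry uses a plural and may only say which OCI-R score counts. This is a fair reading, and it narrows the conflict to one ambiguous sentence plus total score versus subscale. It does not remove the conflict, and it is the reading under which Benjamini–Hochberg fails to control familywise error.

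**The family may be defined elsewhere.** Pooling all ten is an assumption, and a full protocol or SAP may define the family. Silence on that is not the finding. The MANOVA conflict and the conflicting statements of the primary are in the article itself.

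**MANOVA may be only exploratory.** The Abstract does use the word explore, but it names no other method for the scales, so its reader takes MANOVA as the efficacy analysis.

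**Power is understated.** The model adjusts for baseline. With an assumed baseline correlation of 0.5, the 51% and 20% become 62% and 29%. The levels rise, but the gap remains.

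**Stronger readings that the documents do not support**
- A reader might infer that the primary error rate is simply uncontrolled, at about 11.5%. That figure is a limit requiring three null primaries and near-certain secondaries. At the plan's own d=0.3 for the secondaries it is 5–6%, and with a sole OCI-R primary there is no inflation.
- A reader might infer that power falls from 51% to 20%. That needs only OCI-R to move, whereas the hypotheses expect all ten scales to respond.
- A reader might infer that MANOVA would discard 25 of 200 participants. The 25 is only 200 − 175. No dropout rate is stated, and the Data analysis section plans imputation above 10% missing, which a 12.5% loss would trigger.
- A reader might object separately that "a least significant difference test will be conducted with estimated marginal means to compare changes between groups" without adjustment. With two arms there is one between-group contrast per time point and only two post-baseline times, so this is minor.

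**Conclusion.** The point holds in a limited form. Two things are certain from the text: the Abstract and the Methods name different efficacy analyses, and the article does not settle whether there are three primaries or one, or which OCI-R score is meant.

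The consequence for error control is conditional. Under three primaries and a pooled family of ten, the chance of a false primary claim when all three are null is about 5–6%, 6–11% or at most 9–12%, depending on whether the secondary effects are d=0.3, d=0.5 or very strong (correlation 0 to 0.7). Under a sole OCI-R primary, error is held at or below 5%, and the harm is a threshold that moves between 0.005 and 0.05 with other outcomes, with the loss of power shown above. This should be corrected, but it does not invalidate the trial.

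**What to change.** 1. Replace MANOVA in the Abstract with the mixed model of the Data analysis section.
2. State everywhere that the OCI-R OCD subscale is the OCI-R score analysed.
3. Give the primaries their own family with familywise control. Use Holm across the OCI-R OCD subscale, PHQ-9 and GAD-7, or test the OCI-R subscale alone at two-sided 0.05 if the investigators confirm it is the sole primary. Holm demotes none of the hypothesised primaries.
4. Apply Benjamini–Hochberg only to the seven secondary scales.

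**Cost.** The changes are to wording, made before allocation is revealed for the final analysis and recorded on the registry, where the article says modifications will be described. Holm makes the primary thresholds somewhat stricter than 0.05: in order, 0.05/3 = 0.0167, 0.05/2 = 0.025, then 0.05. At the strictest step, d=0.3 with 100 per arm has about 39% power against 56% at 0.05 (unadjusted t-test). That step is still easier to pass than the 0.005 OCI-R would face in a pooled family of ten if nothing else moved.

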**Discusion:**

The present study may contribute novel data on the efficacy of OCD prevention approaches, leading to the development of an evidence-based OCD prevention program that could alleviate individual and societal burdens associated with OCD.

**Trial registration:**

This trial was approved by the University Ethical Review Authority (937/ 28.11.2023) at Babeș-Bolyai University and is registered on clinicaltrials.gov (ID: NCT06262464).

## Article summary

Strengths and limitations of this study

• First study to develop and validate an OCD prevention program for at-risk adults.

• The program integrates psychological prevention techniques from evidence-based treatments.

• Moderate expected rates of participants dropout

## Background

Obsessive-compulsive disorder (OCD) is one of the most debilitating mental health disorders, with considerable burden on patients, their families, and health services [19]. As a psychiatric disorder, it is characterized by the co-occurrence of recurring, intrusive obsessions that induce substantial distress, along with compulsions—ritualistic behaviors aimed at relieving the distress triggered by the obsessions but ultimately resulting in additional distress and impairment (American Psychiatric Association, 2013). The prevalence estimates vary from 0.7-3% in adults [26],Adam et al., 2011), and 0.25-0.30% in children (Sadler et al., 2017; [17].

OCD has both direct costs, such as medical costs [16, 18], as well as indirect costs, such as work absenteeism due to impaired functionality and lost opportunities for career advancement [9]. One UK study [19] found that the overall cost-of-illness of OCD rises to £5,095,759,464, with an average annual cost-of-illness of £7077 per person.

Worryingly, the COVID-19 pandemic seems to have led to an increase in the incidence of OCD. A systematic review [22] found that both people with and without diagnosed OCD before the pandemic experienced a worsening of OCD symptoms during the pandemic. One study [25] found that participants reported significantly higher OCD scores during the pandemic compared to before the pandemic, as OCD severity increased on all symptom dimensions and the most pronounced change was on the washing dimension. Another review (Cunning & Hodes, 2021) found that the COVID-19 pandemic is associated with a worsening of OCD symptoms in young people and that being in treatment seems to have a protective effect, thus underlining the importance of maintaining mental health services. While we have multiple evidence-based treatments for OCD, there are currently no validated protocols for the prevention of general OCD. This is a major shortcoming, seeing as an effective prevention program for at-risk individuals could constitute a preemptive strike against the high associated costs and burden of living that come with a diagnosis of OCD. Former prevention programs for depression and anxiety usually carried out for adolescents and young adults, have varying rates of efficacy, but are overall considered successful in reducing psychopathological symptoms incidence in time (Conley et al., 207; Werner et al., 2021).

The development and validation of an intervention protocol for the prevention of OCD among at-risk adults, as presented in the ØCD prevention program, are thus paramount. By advancing OCD preventive approaches, this study offers hope for mitigating the long-term consequences of OCD and reducing the associated costs and burden on individuals and society.

### Specific contents of the ØCD prevention protocol

The program involves six sessions and includes established components of CBT [4] and ERP [11], namely: (1) psychoeducation and encouragement to reduce, change, or eliminate anxiety-reducing rituals (1 session), (2) cognitive restructuring by challenging dysfunctional beliefs (2 sessions), (3) behavioral changes by prolonged, imaginal and real-life exposure to distress-provoking stimuli (2 sessions), (4) addressing ways and skills to reduce relevant risk factors (i.e. fear of COVID-19) and to develop resilience factors (i.e. resilience levels, coping skills) and summary and recapitulation (1 session). The six sessions of the 2 weeks program correspond to three treatment modules (3 hours/module). An overview of the content covered in each stage is provided in Table 1.

**Table 1 Tab1:** Description of the ØCD modules and sessions

Module	Session	Session Content
Psychoeducation	Overview of OCD	• • Elicit from participant their understanding of OCD. • • Increase motivation for change through psychoeducation. • • Explain what OCD is and the forms it can take. • • Homework: monitor OCD-related thoughts, feelings, and behaviors.
1. Cognitive approach	2. Identifying obsessive sequences	• Mindfulness exercise (Body Scan) to ensure a relaxed state. • Homework debriefing. • Explain how obsessive sequences take place based on participants’ examples. • Connect obsessive sequences to their corresponding compulsions. Homework: identify obsessive sequences in everyday life.
2. Cognitive approach	3. Perspective and how to change it	• Homework debriefing. • Introduce the concept of perspective. • Explain how perspective can affect the formation and maintenance of the circle of obsessions. • Offer examples as to how changing the perspective can prevent engaging in the obsessive sequence and compulsions. • Introduce the Cognitive ABC model. • Homework: identify three cognitions and apply the Cognitive ABC model.
2. Behavioral approach	4. Exposure and Response Prevention (ERP)	• Homework debriefing. • Revision of the concepts discussed previously. • Discussion about compulsions. • Introduce Exposure and Response Prevention. • Engage participants in an ERP exercise. • Homework: choose a medium-level anxiety situation and apply the ERP steps.
3. Behavioral approach	5. Imaginal exposure and ERP	• Check in with the participants and their progress. • Recapitulate ERP and homework debriefing. • Introduce imaginal exposure. • Imaginal exposure exercise: participants will have 10 minutes to write a scenario about a situation that causes them anxiety. • Participants will monitor thoughts, anxiety levels, safety behaviors and strategies used to prevent engaging in the compulsions. • Homework: vocally record the scenario and listen to it 3-4 times after performing the Body Scan exercise.
3. Summary	6. Values and Committed Action. Summary	• Homework debriefing. • Revision of cognitive and behavioral skills acquired in the intervention. • Introduce Values and Committed Action. • Explain the importance of engaging in behaviors consistent with their values. • Write a values hierarchy and establish the behavioral changes needed to align behavior with values. • Create a maintenance plan for participants to maintain the progress made during the intervention. • Debriefing of the participant's experience in the intervention.

### Aim of the present study

The main objective of the proposed study is to develop and assess the efficacy of the ØCD prevention program in preventing OCD symptoms and reducing associated symptoms versus a waitlist control group. In this single-blind, superior randomized controlled trial, we will evaluate the efficacy of the ØCD prevention program compared with a waitlist. If, as we hypothesize, the ØCD prevention program demonstrates superiority compared to a control group, it has the potential to increase the variety of evidence-based intervention options for adults at risk of developing OCD.

We hypothesize that the ØCD prevention program will be superior to a control group in the reduction of OCD symptoms as measured by the Obsessional Compulsive Inventory – revised form (OCI-R; [10]), depressive symptoms (Patient Health Questionnaire-9,PHQ-9; [20]), and anxiety symptoms (Generalized Anxiety Disorder-7,GAD-7; [29]). The intervention also covers the cognitive component of OCD, so we expect a reduction in obsessive beliefs (The Obsessive Beliefs Questionnaire,OBQ-44; [24]) and automatic thoughts (Automatic Thoughts Questionnaire,ATQ; Steven & Phillip, 1980). We also expect a reduction in experiential avoidance levels (The Brief Experiential Avoidance Questionnaire; EAQ; Gamez et al., 2014), intolerance of uncertainty (Intolerance of Uncertainty Scale: IUS; [5]), and general distress (General Health Questionnaire-12,GHQ; [15]). As for protective factors, we expect an increase in resilience (Resilience Scale for Adults,RSA; [13]) and quality of life (WHO Quality of Life - BREF,WHOQOL-BREF; [28]).

## Methods

### Study design and ethical aspects

We will conduct a single-blind (blinded outcome assessors), randomized (1:1), controlled, parallel-group, superiority trial comparing the ØCD prevention program with a control group (waitlist) for adults at risk of OCD. The study is registered on clinicaltrials.gov (ID: NCT06262464). All quality and safety aspects will be regularly monitored by an external party: the University Ethical Review Board, and by the financing authority of the project (National Authority for Scientific Research). The study has been approved by the University Ethical Review Authority (937/28.11.2023). Potential protocol modifications will be described in detail on clinicaltrials.gov. We used the SPIRIT reporting guidelines [6].

Participants will be asked to provide informed consent before baseline assessment. They will receive detailed information about the study and their right to withdraw from the study without the obligation to give reasons. We do not expect major relevant risks for participants during the study, or after the study is completed. The time burden for the participants will be a reasonable amount. The data collection and storage will be conducted according to GDPR legislation, and all personal data will be securely stored on the University’s encrypted servers, following the set data management guidelines.

### Sample size

G*Power was used for the sample size calculation and, following an effect size of d=0.3 with a n alpha level of α = 0.05 and power of 0.95, a sample size of 175 was suggested. Based on this power analysis and expected drop-out rates, we aim for 200 participants (100 per treatment arm). The Consolidated Standards of Reporting Trials flow chart of the trial is shown in Figure 1.

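### The stated 175 participants do not follow from d=0.3, alpha 0.05 and 95% power in a two-arm trial, which needs 580 (two-sided); unadjusted power at d=0.3 is about 51%

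*Protocol article*

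**What the plan says.** The Sample size section attributes the calculation to G*Power and gives an "effect size of d=0.3 with a n alpha level of α = 0.05 and power of 0.95, a sample size of 175 was suggested". It then allows for losses: "Based on this power analysis and expected drop-out rates, we aim for 200 participants (100 per treatment arm" is the stated target. Because 200 is a total across both arms and is built on 175, the 175 must also be a total.

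The section on study design and ethical aspects describes a 1:1, parallel-group superiority trial with two conditions. The Data analysis section tests the time-by-treatment interaction with the "Benjamini–Hochberg procedure (two-sided p < 0.05" level, and plans mixed models with adjustment for baseline values.

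**The concern.** A standardised difference of 0.3 is small, and 95% is a demanding power. For two parallel arms that combination calls for several hundred participants, so 175 in total is implausibly low on its face.

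The stated power governs how a null result will be read. A trial with 95% power for d=0.3 that finds nothing is strong evidence against an effect of that size. If the power is far lower, a null result says much less, and readers who rely on the Sample size section would be misled.

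**Working it through.** **Inputs from the article.** d=0.3, alpha 0.05, power 0.95, N=175 in total and a target of 200 (Sample size); two arms, 1:1 (study design); two-sided testing and baseline adjustment (Data analysis). The Sample size section does not say whether its test is one- or two-sided, so both are shown.

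**Step 1. Try to reproduce 175.** The normal approximation per arm is n = 2 × [(z for alpha + z for power) / d]².

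- Two-sided: 2 × [(1.960 + 1.645)/0.3]² = 288.8, so 289 per arm. The exact noncentral t calculation gives 290 per arm, **580 in total**.
- One-sided: 2 × [(1.645 + 1.645)/0.3]² = 240.5, so 241 per arm. Exact: 242 per arm, **484 in total**.

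The stated total is short by a factor of 580/175 = 3.3 (two-sided) or 484/175 = 2.8 (one-sided). Rounding or sidedness cannot explain this.

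**Step 2. Power at d=0.3 for the planned numbers.** Unadjusted two-sided t-test, noncentrality = d × √(n₁n₂/(n₁+n₂)).

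- 175 analysed (87 and 88): 0.3 × √(87×88/175) = 1.98, against a critical value of 1.97. Power **50.5%**.
- 200 analysed (100 and 100): 0.3 × √50 = 2.12, against 1.97. Power **56.0%**.
- One-sided: 63.0% and 68.1%.

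**Step 3. What 175 can detect.** Unadjusted, two-sided 0.05: d=0.43 at 80% power, 0.49 at 90% and 0.55 at 95%.

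**Step 4. Baseline adjustment.** With baseline–outcome correlation r, the effective standardised difference is d/√(1−r²). The article gives no r, so the values below are assumptions.

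| Assumed r | Effective d | Power, 175 analysed | Power, 200 analysed |
|---|---|---|---|
| 0 | 0.300 | 51% | 56% |
| 0.5 | 0.346 | 62% | 68% |
| 0.6 | 0.375 | 69% | 75% |
| 0.7 | 0.420 | 79% | 84% |

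With 175 analysed, 95% power requires r of about 0.84, since 0.3/√(1−0.84²) = 0.553, just above the 0.55 of Step 3.

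**Step 5. Where might 175 come from?** In an F-test with noncentrality f²N, f=0.3, alpha 0.05 and 95% power:

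- 1 numerator df (the two-arm contrast): N=147, or 148 with equal arms.
- 2 numerator df: **N=175**, exactly.
- 3 numerator df: N=195.

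Other settings come close. A within-between interaction with f=0.15 gives 174 (three time points, correlation 0.25) or 176 (two time points, correlation 0.4). Taking 175 as a per-arm figure, d=0.3 gives 80% power (175 by normal approximation, 176 exactly).

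**The case against.** The strongest reply is that the planned analysis is not an unadjusted t-test. The Data analysis section adjusts for baseline, so a reader who concludes that the trial's true power at d=0.3 is about 50% goes further than the documents allow. This part stands. About 51% is the unadjusted figure, and the power of the planned model is higher by an amount that cannot be fixed without a correlation. It does not restore the stated 95%, which would need r of about 0.84 with 175 analysed. The Sample size section claims no such credit.

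A second reply is that some repeated-measures setting may lie behind 175. The article does plan a time-by-treatment interaction, so this cannot be excluded. But the settings found need correlations that are not stated, and f=0.15 on that scale is not a 0.3 SD difference between arms. In a two-by-two layout, interaction cell effects of ±0.15 SD amount to a between-arm difference in change of 0.3 + 0.3 = 0.6 SD. The reading of 175 per arm at 80% power conflicts with the stated power of 0.95 and with 100 per arm.

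It is also tempting to infer that 0.3 was entered as Cohen's f and that the trial was therefore really sized for d=0.6. The documents do not support this. They never mention f. The exact match at 175 needs 2 numerator df, whereas f=0.3 equals d=0.6 only for two equal groups (1 df), where N would be 147–148 and 175 would give 97.7% power. Entering 0.3 as f with 2 numerator df remains one possible explanation and is inference only.

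Finally, the article may leave the test family and other settings to a full protocol that is not shown. That is accepted, and their absence is not part of this point. The point is that the stated figures do not agree with each other.

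**Conclusion.** The power statement is wrong as written for a 1:1 two-arm comparison. The stated inputs require 580 participants two-sided (484 one-sided), not 175. With 175 analysed, power at d=0.3 is about 51% unadjusted and 62% to 79% for assumed baseline correlations of 0.5 to 0.7. With all 200 analysed, the corresponding figures are 56% and 68% to 84%.

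These figures assume a single comparison between arms at 0.05, equal variances and d defined on the outcome SD. They take no account of the Benjamini–Hochberg adjustment across outcomes. The 175 analysed corresponds to a loss of 25/200 = 12.5%, which is implied by the two totals and not stated.

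The finding does not mean that the trial must enrol 580. It means that the published power claim must be brought into line with the sample actually planned.

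**What to change.** Keep the target of 200 and replace the power statement in the Sample size section, and in the registry wherever it is repeated. For example: *With 175 analysable participants the trial has 80% power for d=0.43 and 95% power for d=0.55 (two-sided 0.05, unadjusted); power for d=0.3 is about 51%.* If credit for baseline adjustment is claimed, give the adjusted power together with the correlation assumed.

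Do not insert a sentence saying that f=0.3 is equivalent to d=0.6. On the two-arm contrast that gives 147–148, so it would add a second statement that does not reproduce 175.

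The cost is one paragraph of text. No further participants are needed, which matters because 121 had already been randomised at submission (Trial status). The article already commits to describing modifications on the registry. The downside is that the stated power becomes less favourable.
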